## Abstract

**Background:**

In Canada, the majority of HIV-positive pregnant women receive combination antiretroviral therapy that includes a ritonavir-boosted protease inhibitor to prevent mother-to-child HIV transmission. However, protease inhibitor-based combination antiretroviral therapy has been associated with increased rates of preterm, low birth weight, and small for gestational age births. Our previous experimental findings demonstrate that protease inhibitor use during pregnancy is associated with decreased progesterone levels that correlate with fetal growth, and that progesterone supplementation can improve protease inhibitor-induced fetal growth restriction. We hypothesize that HIV-positive pregnant women who receive protease inhibitor-based combination therapy may also benefit from progesterone supplementation during pregnancy.

**Methods/design:**

In order to test this hypothesis, we have designed an open-label, multi-centre, randomized controlled (parallel group) pilot trial. The initial goal of this trial is to test feasibility and acceptability of our intervention. Forty HIV-positive pregnant women who are either on, or intending to start or switch to a boosted protease inhibitor-based combination antiretroviral regimen will be enrolled from six sites across Ontario, Canada. Twenty-five women will be randomized to self-administer natural progesterone (Prometrium, 200 mg) vaginally every night starting between gestational week 16 and 24 until week 36, and 15 women will be randomized to no intervention. While the participants and treating physicians will not be blinded, the laboratory personnel performing the biochemical and morphological evaluations will be blinded to ensure unbiased evaluation. The primary outcome of the pilot study is the feasibility of enrolment as measured by the recruitment rate and patient-reported reasons to decline participation. Secondary outcomes in participants include safety, acceptability, and adherence to progesterone supplementation.

**Discussion:**

Given the safety of intravaginal progesterone and its current use in the general obstetrical population to prevent recurrent preterm delivery, this pilot study will provide data to determine the feasibility of a larger randomized controlled trial to assess the impact of this intervention on improving neonatal health in the context of HIV-positive pregnancies.

**Trial registration:**

ClinicalTrials.gov, NCT02400021

## Background

### Preventing perinatal HIV transmission

Combination antiretroviral therapy (cART) is recommended for all HIV-positive pregnant women for the prevention of mother-to-child HIV transmission and for optimal maternal health. Given the results of recent studies on the health benefits of early cART initiation [1], HIV-positive women are increasingly initiating cART before conception or early in pregnancy. Furthermore, data suggest that earlier initiation of therapy in pregnancy is associated with lower rates of perinatal transmission consequent to prolonged suppression of viral load during pregnancy [2–4]. Since the safety of some newer agents in pregnancy is unknown, it is typical practice to switch cART to one of the guideline-recommended combinations prior to a planned pregnancy. The majority of HIV-positive pregnant women in Canada receive a cART regimen that includes a boosted protease inhibitor (PI) [5].

### The potential risk of protease inhibitor-based combination antiretroviral therapy in pregnancy

Although controversial and often complicated by multiple confounders, data from numerous studies suggest an association between PI-based cART and preterm, low birth weight, and small for gestational age births [6–29]. Preterm birth and low birth weight are significant factors contributing to infant morbidity and mortality, and have been associated with severe short-term and long-term adverse health and social outcomes including increased risk of developmental delay in children [30–35], and higher risk for developing chronic ailments such as diabetes, heart disease, and asthma later in life [36–39].

### Declining progesterone levels as a potential mechanism for the impact of protease inhibitors on birth outcomes

We have previously reported experimental findings demonstrating that PI use during pregnancy is associated with decreased progesterone levels that correlate with fetal growth, and that progesterone supplementation can improve PI-induced fetal growth restriction [40]. Exposure of a human placental cell line to PIs (atazanavir, lopinavir, ritonavir), but not nucleoside reverse transcriptase inhibitors (NRTIs; zidovudine, lamivudine) or a non-NRTI (NNRTI; nevirapine), resulted in decreased progesterone production. In an animal model of pregnancy, lower progesterone levels were detected in mice exposed to PI-based cART (ritonavir-boosted lopinavir) but not in those exposed only to the NRTI backbone. Moreover, the change in progesterone levels was associated with smaller fetuses and other adverse birth outcomes. To establish a direct relationship between progesterone levels and birth outcomes, PI-based cART exposed mice were supplemented with natural progesterone throughout their pregnancy. Progesterone supplementation significantly increased fetal weight in these mice.

Consistent with these data, we have also observed lower progesterone levels at gestational weeks 25–28 in HIV-positive pregnant women exposed to PI-based cART compared to HIV-negative pregnant women. Progesterone levels in the HIV-positive women were significantly correlated with birth weight percentile [40].

### Study rationale and objectives

In the general population, progesterone supplementation is widely used in pregnancy for the prevention of recurrent preterm birth [41, 42]. Progesterone supplementation in pregnancy is well tolerated and considered safe [41, 43–47]. HIV-positive women have higher rates of preterm birth and low birth weight that may be magnified by the use of PIs. Based on our pre-clinical and clinical findings, we hypothesized that HIV-positive pregnant women who receive PI-based cART might also benefit from progesterone supplementation during their pregnancy.

The primary objective of this pilot study is to determine the feasibility of enrolling HIV-positive women on PI-based cART during pregnancy into a randomized clinical trial of progesterone supplementation. Secondary objectives include determining preliminary information on the safety, acceptability, compliance, and barriers to adherence to progesterone supplementation during pregnancy for HIV-positive women. The data will also be used to establish estimates of the standard deviation and the intra-patient correlation coefficient of progesterone levels during pregnancy in order to inform the design of a larger clinical endpoint study.

## Methods/design

### Study design and intervention

This is an open-label, multi-centre, controlled pilot trial in which 40 HIV-positive pregnant women on PI-based cART will be randomized into two groups with an allocation ratio of 5:3. Group A will self-administer intravaginal progesterone (Prometrium, 2 × 100 mg capsules) once every night before bed starting between gestational week (GW) 16–24 until GW36, while group B will receive no intervention (see Fig. 1 for a schematic of the study design).

**Fig. 1 Fig1:**
[figure not shown]
Schematic of study design

### Study setting

Recruitment will take place at six study sites in Ontario, Canada: the Toronto General Hospital Immunodeficiency clinic, the obstetrical clinic at Mount Sinai Hospital, the obstetrical clinic at St. Michael’s Hospital, the Maple Leaf Medical clinic, the obstetrical clinic at Sunnybrook Health Sciences Centre, and the Infectious Diseases Care Program at St. Joseph’s Health Care London. All HIV-positive, pregnant women attending or referred to one of the study centers during the trial will be assessed for eligibility and participation, and those who consent to the study will be followed at the site at which recruitment occurs.

### Participant eligibility criteria

To be considered for enrollment in this pilot study, the following inclusion criteria must be fulfilled:Female; 16 years or olderDocumented HIV-1 infectionOn stable, or initiating, cART containing either ritonavir-boosted lopinavir (LPV/r), ritonavir-boosted atazanavir (ATZ/r), or ritonavir-boosted darunavir (DRV/r)Pregnant up to 24 weeks gestational ageSingleton pregnancyAbility to give informed consent

Participants are excluded based on the following criteria:Hypersensitivity or allergy to soya or peanut (non-active ingredient supplement in Prometrium)Contraindications to intravaginal progesterone use including:Documented hypersensitivity to PrometriumActive or history of breast cancerActive or history of arterial thromboembolic disease (e.g., stroke, myocardial infarction, coronary heart disease)Active or history of venous thromboembolism (e.g., deep venous thrombosis or pulmonary embolism) or active thrombophlebitisAny prior neoplasia, except for skinAbnormal vaginal bleeding
Known lethal fetal anomalyAny contraindication to continuation of pregnancyInability to communicate in EnglishPrior participation in this trialPrior experience with intravaginal progesterone administration

### Outcomes

The primary outcome is feasibility. The proportion of HIV-positive, pregnant women who are approached and screened but do not meet eligibility criteria will be recorded, as well as the proportion of women who meet eligibility criteria but decline to participate. Data will be collected on the gestational age at screening and enrollment. Data will also be collected on the reasons for non-participation. This information will be used to determine the number of centers that will be required for timely recruitment of a larger randomized control trial (RCT). A consent rate of less than 60 % among women that meet eligibility criteria would be grounds for not moving forward with a larger RCT in this setting.

Secondary outcomes include safety, acceptability, compliance, and barriers to adherence. Safety and tolerability will be assessed through questionnaires administered to participants during the study, and by recording adverse events (AE) using the Division of AIDS (DAIDS) Table for Grading the Severity of Adult and Pediatric AEs and Addendum 1 Female Genital Grading Table for Use in Microbicide Studies [48]. AEs of all grades will be recorded, and the proportion of participants who report AEs will be compared between study arms. Any grade 4 AE or severe adverse event (SAE) attributed to progesterone supplementation would be grounds for not moving forward with a larger RCT. Standardized questions will capture group A’s experience with progesterone self-administration and information on local irritation or discomfort. Study acceptability will be measured by capturing whether participants are willing to be randomized to the no intervention arm, and participants’ overall impression of the study. Compliance to treatment will be assessed in group A via capsule count and through a standardized compliance questionnaire at each follow-up visit. Barriers to adherence to progesterone supplementation, and to study follow-up visits, will be assessed using standardized questionnaires.

Exploratory outcomes include (a) changes in serum/urine progesterone levels during pregnancy, (b) correlation of serum/urine progesterone levels with birth weight, birth weight percentile, and gestational age at birth, (c) the relationship between degree of adherence to progesterone supplementation with birth weight, birth weight percentile, and gestational age at birth, (d) the distributions of birth weight and gestational age at birth, including low birth weight (< 2500 g) and small for gestational age births, (e) serum and cell levels of sex steroids, angiogenic, vasoactive, and inflammatory factors, and factors associated with placentation, placenta dysfunction, preterm delivery, and fetal growth restriction, (e) placenta histology, and (f) serum PI drug concentrations.

This study will also provide information on the standard deviation of the change in progesterone levels, and the intra-patient correlation coefficient among repeated progesterone levels during pregnancy to inform the design of a larger RCT.

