Follow-up visits occur monthly for both study groups. Participants undergo a targeted clinical evaluation. Assessment of safety includes clinical observation and monitoring of laboratory measurements. Symptoms, physical exam findings, and laboratory findings are graded based on the DAIDS Table [48]. At each monthly visit, all participants complete a questionnaire to report any adverse events they may have experienced in the past month. For group A, study medication compliance is assessed at each monthly visit through a capsule count. A compliance questionnaire captures how frequently group A participants have been taking the progesterone and a second adherence questionnaire is provided if participants miss dose(s) to record the reason(s) they missed their medication. If any of the participants miss a follow-up visit, a questionnaire records reasons why they missed their appointment.

At delivery, a clinical and laboratory evaluation of the infant (e.g., birth weight, gestational age at birth, sex, umbilical cord gas results, and Apgar score) is performed according to standard of care. Maternal blood, cord blood, placenta, umbilical cord, and membrane tissue samples are also collected to meet exploratory objectives.

An exit visit occurs 4–8 weeks post-delivery. During this visit, participants undergo a targeted clinical evaluation and complete a short exit questionnaire that allows participants to reflect on their involvement in the study and provide suggestions for the study moving forward with a larger RCT.

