### Data recording and adverse event reporting

Data recording will occur using a study case report form (CRF). Data from the CRF will be consolidated into a secure, password-protected internet-enabled database with built-in quality checks.

Any AE that occurs between the time a study participant signs the informed consent form and the time she departs the study at the end of the final follow-up visit (or at the time of early discontinuation from the study for any reason) will be captured and recorded. The start date, the stop date, the severity of each reportable event, and the judgment of the AE’s relationship to the study medication/intervention will also be recorded. All serious adverse events (SAEs) occurring during the course of the study will be reported to the project manager within 24 h of the site becoming aware of the event. Adverse events that had previously been reported by the study subject will also be reassessed for duration, intensity, and possible reoccurrence. All AEs and SAEs will be followed until resolution or until the investigator and the clinical/medical monitor are in agreement that the AE/SAE has stabilized and no more follow-up is required. If an SAE is ongoing at the time a participant discontinues/completes the study, the SAE will be followed until the investigator agrees that the event is satisfactorily resolved, becomes chronic, or that no further follow-up is required.

A Data and Safety Monitoring Board (DSMB) will review the AE/SAE reports submitted by the sponsor/central study coordinator. The DSMB might conclude the study early if unacceptably high rate of AE/SAE is observed.

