### Statistical analysis

The primary endpoint is the proportion of enrolled participants out of all eligible patients. Qualitative information on the reasons to decline participation will be collected and summarized.

Secondary endpoints include the safety of progesterone supplementation during pregnancy for HIV-positive women as measured by the frequency and severity of AEs in group A and group B. Compliance to progesterone supplementation will be assessed in group A by the proportion of missed doses out of the total prescribed doses per participant. The acceptability of the intervention and barriers to adherence to progesterone supplementation will be recorded for participants in group A. For both group A and B participants, barriers to appointment attendance will be captured and acceptability of the entire study will be assessed in an exit questionnaire.

The relationships between progesterone levels (serum or urine) at baseline, 1 week post-baseline, GW25–GW28 or GW33–GW36 and birth weight, birth weight percentile, and gestational age at birth will be assessed with Spearman’s rank correlation. Serum/urine progesterone levels will be compared between women with and without an AE/SAE using descriptive statistics, if sufficient numbers of events occur. The levels of biomarkers will be compared between the two arms at baseline, 1 week post-baseline, GW25–GW28, GW33–GW36 and delivery visits using descriptive statistics and graphical methods. Qualitative assessment of placenta morphology will be performed blinded to the arm allocation and birth outcome.

Although, this pilot study is not powered for subgroup analyses, qualitative assessment of the impact of race, age, previous adverse pregnancy outcome on enrollment into study, acceptability of progesterone, and adherence will be conducted where possible.

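### The only between-arm AE proportion the protocol names is any AE of any grade with no exposure window, so events after progesterone stops can dilute it; the past-month recall period can also skip a month

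*Protocol article*

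**What the plan says.** All references are to the protocol article.

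- **Measure.** Outcomes: "AEs of all grades will be recorded, and the proportion of participants who report AEs will be compared between study arms". The sentence sets no limit by grade, relatedness or period.
- **Endpoint.** Statistical analysis describes safety "as measured by the frequency and severity of AEs in group A and group B", again without a period.
- **Capture window.** Data recording and adverse event reporting covers "Any AE that occurs between the time a study participant signs the informed consent form and the time she departs the study", that is, to the final follow-up visit or early discontinuation. Participant timeline and monitoring places that final visit: "An exit visit occurs 4–8 weeks post-delivery".
- **Exposure.** Study design and intervention has group A take progesterone "once every night before bed starting between gestational week (GW) 16–24 until GW36".
- **Data held on each event.** The AE section lists the items to be kept (sentence cut short here): "The start date, the stop date, the severity of each reportable event, and the judgment of the AE’s relationship to the study medication/intervention will also".
- **Monthly question.** At each monthly visit "all participants complete a questionnaire to report any adverse events they may have experienced in the past month". If a visit is missed, a separate questionnaire asks why it was missed.
- **Progression rule.** Outcomes makes a grade 4 AE or an SAE attributed to progesterone a reason not to proceed to the larger trial.

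**The concern.** Preliminary safety information is a secondary objective, and group B is the only untreated comparison. The recognised maternal side effects listed in the Discussion include headache, nausea and breast tenderness, which are also ordinary complaints of pregnancy. Judged relatedness in an open-label trial separates drug effect from background poorly for such events. A comparison with group B over the period when group A is taking the drug does it better.

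The stated proportion counts a woman once, for any event. If the capture window is also the analysis window, a woman whose first event comes after GW36 counts the same as one who had an event on drug. Shared off-drug events therefore pull the two proportions together, and a small difference could be read as reassurance.

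The recall wording is a separate, smaller weakness. The AE section promises that any AE will be captured, but a question limited to the past month does not reach back across a skipped visit.

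**Working it through.** **1. Plan's own figures.** 40 × 5/8 = 25 and 40 × 3/8 = 15, which matches the Abstract. The protocol gives no AE rate, test, alpha or power for safety, so there is no safety figure to reproduce.

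**2. Share of the window off drug.** On-drug time is 36 − 24 = 12 to 36 − 16 = 20 weeks. Assume delivery at GW40. Off-drug time is then (40 − 36) + 4 = 8 to (40 − 36) + 8 = 12 weeks.

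| Start | Exit after delivery | Observed (weeks) | Off drug (weeks) | Share off drug |
|---|---|---|---|---|
| GW16 | 4 weeks | 28 | 8 | 29% |
| GW16 | 8 weeks | 32 | 12 | 38% |
| GW24 | 4 weeks | 20 | 8 | 40% |
| GW24 | 8 weeks | 24 | 12 | 50% |

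With delivery at GW37 instead, the share runs from 5/25 = 20% to 9/21 = 43%.

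**3. Dilution.** Let a and b be the probabilities of at least one AE up to GW36 in groups A and B, and q the probability of at least one AE after GW36. Assume q is the same in both arms and independent of earlier events. Over the whole window:

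A: 1 − (1 − a)(1 − q); B: 1 − (1 − b)(1 − q); difference = (a − b)(1 − q).

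Any q above zero shrinks the contrast. How much depends on q, which the documents do not give.

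**4. Illustration.** Assume b = 0.50 and a progesterone-caused risk of 0.40, so a = 1 − 0.50 × 0.60 = 0.70. Power is for an assumed two-sided 5% Fisher test at 25 versus 15.

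| q | A | B | Difference | Fisher power |
|---|---|---|---|---|
| 0 (events to GW36 only) | 70% | 50% | 20 points | 0.20 |
| 0.3 | 79% | 65% | 14 points | 0.12 |
| 0.5 | 85% | 75% | 10 points | 0.08 |
| 0.7 | 91% | 85% | 6 points | 0.06 |
| 0.9 | 97% | 95% | 2 points | 0.02 |

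**5. Second illustration, constant event rate.** Let m be the assumed background proportion of women with an AE per 4 weeks, giving a weekly rate w = −ln(1 − m)/4. Take 16 weeks on drug, 10 weeks off, and an on-drug rate in group A 1.5 times background. Then b = 1 − exp(−16w), a = 1 − exp(−24w) and q = 1 − exp(−10w).

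| m | q | To GW36, A vs B | Whole window, A vs B |
|---|---|---|---|
| 0.2 | 0.43 | 74% vs 59% (15 points) | 85% vs 77% (8 points) |
| 0.3 | 0.59 | 88% vs 76% (12 points) | 95% vs 90% (5 points) |
| 0.5 | 0.82 | 98% vs 94% (5 points) | 99.7% vs 98.9% (1 point) |

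The last row shows that a high background compresses the any-grade contrast even within the exposure window. That is the reason for a grade 2 or higher row in the added table.

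**6. Recall.** If one monthly visit is missed, about two months separate the completed visits, and a past-month question covers one of them. The missed-visit questionnaire, as described, asks for reasons and not for events.

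**The case against.** The strongest reply is that the capture window is not the analysis window. The AE section says when events are collected; neither Outcomes nor Statistical analysis says over what period proportions are compared. This is a condensed article, and a statistical analysis plan that is not shown may define on-treatment tables. That stands as a limit: the dilution follows only if the stated proportion is read with the stated capture window. It is still the only between-arm AE proportion named, and nothing in the text restricts it.

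A reader might go further and infer that labour and postpartum events will fill the measure, bring it near 100% in both arms and mask harm. The documents do not support that. They give no AE rates and do not say that ordinary delivery or postpartum occurrences count as AEs. At m = 0.2 above, the whole-window figures are 85% and 77%, not a ceiling. Frequency and severity are also summarised by arm. Dates, grades and relatedness are recorded, and a safety board reviews reports. Group A is asked separately about local irritation. The progression rule rests on attributed grade 4 AEs and SAEs, not on the any-AE proportion. These offset the problem only in part: the local questions have no group B counterpart, and the progression rule is not designed to detect low-grade effects.

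It is also fair that the full window has its own value. The Discussion ties progesterone to uterine quiescence and the onset of labour, so events around delivery may be relevant to safety and should not be dropped. The time between consent and randomisation appears short and adds little.

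On recall, the questionnaire itself is not shown, and clinical evaluation at visits may recover some events. The described wording nevertheless leaves a gap that the AE section's promise does not allow for.

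**Conclusion.** The point holds as a modest design weakness. The one named between-arm safety proportion is any AE of any grade with no exposure window. Read with the capture period, it takes in off-drug time amounting to about 29% to 50% of observation if delivery is at GW40. The contrast shrinks by (1 − q), given an off-drug risk that is common to both arms and independent of earlier events. The value of q, and so the points lost, cannot be taken from the documents. A ceiling near 100% is possible but not shown, and masking of harm is too strong a reading given the other safety summaries.

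Pilot size limits formal inference more than the window does. In the first illustration power is only 0.20 even with no dilution. In the most favourable case tried (control risk 0.30, caused risk 0.60) it is 0.69 up to GW36 and 0.26 at q = 0.5. The value of the change is therefore a clearer descriptive estimate to carry into the larger trial, not a usable test.

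The recall gap stands as a separate small inconsistency between the monthly questionnaire and the commitment to capture any AE.

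**What to change.** 1. Keep the full-window AE and SAE summary. In addition, tabulate by arm the proportion of women with a new or worsened AE from randomisation to GW36, or to delivery if earlier, using the same window in both arms. Show it overall and for grade 2 or higher, and list later events separately by arm.
2. Change the monthly questionnaire's recall period from the past month to the time since the last completed study visit.

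Cost: one extra table built from start dates and grades already recorded, and one line of the questionnaire. Recall is longer, and so less reliable, after a missed visit. The added table does not make the comparison confirmatory at 25 versus 15 and should be labelled descriptive. If the statistical analysis plan already contains such a table, a cross-reference from Outcomes is enough for the first item.

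### Prompted questions on local irritation are described for group A only, so the between-arm comparison of AE proportions could be inflated in group A if those answers are counted as AEs

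*Protocol article*

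**What the plan says.** All of this is in the protocol article, under Methods/design.

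- **Outcomes, sources of safety data.** "Safety and tolerability will be assessed through questionnaires administered to participants during the study", and by recording AEs graded with the DAIDS table and its female genital addendum. Neither source is limited to one arm.
- **Outcomes, comparison.** All grades count, and "the proportion of participants who report AEs will be compared between study arms".
- **Outcomes, group A items.** Standardized questions cover group A's "experience with progesterone self-administration and information on local irritation or discomfort". The sentence names group A alone and stands within the safety text, just before study acceptability is taken up.
- **Participant timeline and monitoring.** "Follow-up visits occur monthly for both study groups", with a targeted clinical evaluation. "At each monthly visit, all participants complete a questionnaire to report any adverse events they may have experienced in the past month". Symptoms and examination findings are graded on the DAIDS table.
- **Data recording and adverse event reporting.** Every AE from consent to study exit is to be captured, with no exception by the route through which it came to light.
- **Statistical analysis.** Safety is a secondary endpoint "as measured by the frequency and severity of AEs in group A and group B". Acceptability of the intervention and barriers to adherence are listed separately, for group A. No test, significance level or power is given for AEs.

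**The concern.** A comparison of AE proportions is fair only if both arms have the same chance of having an event noticed and written down. Here one arm has an extra, targeted route to a class of events that the plan itself intends to grade. A mild symptom that a woman would not volunteer on a general questionnaire may be disclosed when she is asked about it by name. If that disclosure becomes a recorded AE, the comparison mixes any effect of progesterone with an effect of asking.

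The trial is open label for participants and physicians, so nothing offsets this, and awareness of treatment may push reporting the same way. The distortion would fall mainly on local tolerability, which is what one most wants to learn about a vaginal product. The Sample size section names safety concerns among the things this pilot should inform before a larger trial.

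**Working it through.** **Arm sizes.** The Abstract gives 25 and 15 women. The 5:3 allocation of 40 reproduces this: 40 × 5/8 = 25 and 40 × 3/8 = 15.

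**Do the prompted answers reach the compared proportion?** No sentence says so. Four features point towards yes: the group A questions stand in the safety text; safety is assessed through questionnaires; a genital grading table is adopted; and any AE is captured whatever its source. Two point towards no: a common AE questionnaire is described for everyone, and the Statistical analysis section lists group A's acceptability data apart from AEs. Both cases are therefore worked.

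**Case 1: answers not counted.** The excess from this source is 0.

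**Case 2: answers counted, no drug effect.** Let p0 be the proportion reporting an AE through the common route, equal in both arms. Let q be the proportion, among women with no AE by that route, who acquire one because of the group A questions. Then

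- group B: p_B = p0
- group A: p_A = 1 − (1 − p0)(1 − q)
- excess: p_A − p_B = (1 − p0) × q

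The article gives neither p0 nor q, so both are assumed over a range. Each cell shows the excess in percentage points. In brackets is the chance that a two-sided Fisher exact test at 0.05, with 25 vs 15 women, would reject. The test and level are also assumptions, used only as a yardstick.

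| p0 | q = 0.1 | q = 0.2 | q = 0.3 | q = 0.5 |
|---|---|---|---|---|
| 0.3 | 7 (0.047) | 14 (0.102) | 21 (0.198) | 35 (0.507) |
| 0.5 | 5 (0.039) | 10 (0.066) | 15 (0.116) | 25 (0.307) |
| 0.7 | 3 (0.035) | 6 (0.047) | 9 (0.067) | 15 (0.145) |
| 0.9 | 1 (0.022) | 2 (0.028) | 3 (0.035) | 5 (0.056) |

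With q = 0 the excess is 0 and the rejection rate is 0.031 at p0 = 0.3, 0.5 and 0.7, and 0.018 at p0 = 0.9.

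**One worked example, all rates assumed.** Suppose 25 % of women in both arms have a local symptom, all captured when prompted and 40 % when not, and 60 % have some other AE independently.

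- Local symptoms recorded: 25 % in A; 0.25 × 0.40 = 10 % in B; a 15-point gap.
- Any AE: A = 1 − 0.40 × 0.75 = 70 %; B = 1 − 0.40 × 0.90 = 64 %; a 6-point gap. This matches the formula with p0 = 0.64 and q = 0.06/0.36 = 0.17.
- Standard error of that gap: √(0.70 × 0.30/25 + 0.64 × 0.36/15) = √(0.0084 + 0.01536) = 0.154, or about 15 points.

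In this example the artefact in the any-AE proportion is well within sampling noise. For local symptoms taken alone it is more than twice as large (15 vs 6 points).

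**The case against.** The strongest reply is that the article already separates the two kinds of data. It names a common AE instrument, on which "all participants complete a questionnaire to report any adverse events they may have experienced in the past month", and the Statistical analysis section lists acceptability apart from AEs. The irritation items are paired with self-administration and may be meant as product-acceptability questions. On that reading there is no bias from this source. The contents of the common questionnaire are not shown and may include genital symptoms, and a condensed article need not reproduce its forms. Some of the group A items concern self-administration and cannot be put to group B.

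Much of this stands. A reader might infer that group A is bound to show more AEs. The documents do not support that: whether prompted answers are counted is not stated, group B has its own monthly questionnaire and evaluation, and with 25 vs 15 women any excess holds only on average. A reader might also infer that the decision to proceed is biased against progesterone. The stated safety criterion is a grade 4 AE or SAE attributed to progesterone, which questions on irritation would hardly move. The other stated criterion is the consent rate. The DSMB may act on a high AE rate, but no between-arm rule is given.

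What does not stand is that this is merely detail left to a fuller document. The article itself restricts the irritation questions to group A, places them in the safety text and compares all-grade AE proportions between arms.

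**Conclusion.** The concern holds in conditional form. The plan as described gives group A a prompted route to local symptoms that it does not describe for group B, and it compares the proportion reporting AEs of any grade. If the prompted answers are recorded as AEs, which the text makes likely but does not state, group A is expected on average to record more, chiefly mild local events, with no drug effect.

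The any-AE excess is (1 − p0) × q: 1 to 5 points if 90 % of women report something anyway, and 7 to 35 points if 30 % do, for q from 0.1 to 0.5. It is nil if the answers are kept apart. These rates are assumptions; the argument also assumes that some women in both arms have local symptoms unrelated to progesterone that they would not volunteer. What is at risk is the reading of the safety comparison, above all local tolerability, and not the stated no-go rule.

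**What to change.** Preferred: put the local-symptom items, such as irritation and discomfort, in the monthly AE questionnaire for both arms, and keep only the self-administration items for group A. This equalises prompting and still allows local symptoms to be compared.

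If the forms cannot change: state that the between-arm AE comparison uses only events from the common questionnaire and the clinical evaluation, and report group A's prompted irritation descriptively. Having women complete the common questionnaire before the group A items would limit carry-over within a visit.

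Either change sets the directly counted prompting excess to 0. Neither removes reporting differences that come from the open-label design. The cost is a few extra items on a form that group B already completes, or one sentence in the Statistical analysis section.
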